# Recruitment process

Participant recruitment will only commence once the study team has ensured that the following approval/essential documents are in place:

1. The main REC, and Health Research Authority (HRA) approval.

2. Final sponsorship and/or confirmation of Capacity and Capability (C&C).

3. Sponsor has conducted the trial initiation procedure.

4. Signed delegation of Duties and Signature Log is completed.

All subjects who wish to enter the study will be screened and consented by the Chief Investigator, or one of the qualified clinicians involved in the study as Clinical Co-investigator.

All pregnant females with CF who are looked after by the Royal Brompton Hospital (RBH) will be approached to assess suitability based on medical notes and interest in taking part in the study. The CI leads the RBH CF Reproductive and Maternal Health Service where potential participants will be identified and provided with study information verbally. After this discussion they will receive a Patient Information Sheet (PIS).

Infants will be identified through the above service, either from mothers who are already pregnant when recruitment opens or those who become pregnant and are expected to deliver within the study timeframes. Parents of infants recently born and below 12 months of age will also be approached. It is anticipated that many of the infants will be born to mothers enrolled in the ‘Mama’ sub-study, but this is not an inclusion criterion. Those infants whose biological father is a person with CF under the care of the RBH Adult CF Service will be identified through the general CF clinics, and fathers given the same PIS.

After the infant is born inclusion/exclusion criteria will be assessed by a paediatrician via phone or video call and if eligibility is met they will be consented to enter the study..

The RBH CF Reproductive and Maternal Health Service have a database of children born to people with CF under their care. This database will allow the study team to locate children who are or will be between three to six years for inclusion in the ‘Midi’ sub-study. Parents of these children will preferably be contacted during their routine clinic visits, with follow up information sent via email and/or phone calls. If there are no scheduled clinic visits upcoming, they will be approached via phone. Furthermore, offspring enrolled in the ‘Mini’ sub-study can also take part in the ‘Midi’ sub-study as/when they reach the appropriate age within the study period.

Should parents be interested in the study, they will receive a PIS for which they will have at least 24 hours to consider whether they want their child enrolled in the study.

# Study procedures and assessments

Section 9.1. and 9.2 describe the procedures for informed consent and screening respectively, which must be carried out before any further assessments for all three sub-studies.

A description of each subsequent sub-study assessment is then described in section 9.3 for ‘Mama’ and section 9.4 for ‘Mini’ and ‘Midi’, with an associated schedule of assessments table.

## Informed consent

Eligible participants (or parents of eligible participants as per ‘Mini/Midi’ sub-studies) will be given a participant information sheet, *via* hand or email, and have a minimum of 24 hours to consider the invitation. Consent to enter the study will be obtained after a full account has been provided of its nature, purpose, risks, burdens and potential benefits, and the participants or parents have had the opportunity to deliberate. If there follows agreement to participate, informed consent will be obtained prior to study entry. The Investigator or designee will explain that the participants are under no obligation to enter the study and that they can withdraw at any time, without having to give a reason.

The consent process will be completed electronically through the REDCap database, or in person if a clinical visit is planned. For participants consented electronically, they will be able to download a copy of their consent form for their own records, The signed e-consent form will be stored in the secure REDCap study archive. A copy will be uploaded to the patient’s electronic medical records. One printed copy will be filed in the Investigator Site File (ISF).

If participants are consented in person, the original signed consent form will be retained at the study site (one filed in the medical notes, and one filed in the ISF). A copy of the signed consent form will also be given to the participant (or parents)*.*Informed consent will be obtained by the Chief Investigator, Principal Investigator and/or a nominated deputy as recorded on Sponsor’s Delegation of Responsibilities Log. All individuals taking informed consent will have received training in Good Clinical Practice (GCP).

## Screening assessments

Subject to receipt of informed consent from participants/parents, the inclusion and exclusion criteria will again be reviewed with the participants/parents and by using their medical notes.

## ‘Mama’ sub-study assessments

### Summary flow chart of study assessments (Table 1)

Assessments that are performed in addition to clinical care are highlighted in grey.

| Study Procedure | Pre-conception | 1^st^ trimester | 2^nd^ trimester | 3^rd^ trimester | 4-8 weeks PP | 6 months PP | 12 months PP | 24 months PP |
| --- | --- | --- | --- | --- | --- | --- | --- | --- |
| Informed consent | X |  |  |  |  |  |  |  |
| Inclusion/exclusion criteria | X |  |  |  |  |  |  |  |
| Demographics | X |  |  |  |  |  |  |  |
| Sputum sample | X | X | X | X | X | X | X | X |
| Clinical Blood tests^2^ | X | X | X | X | X |  | X | X |
| Blood test for CFTRm assay | X | X | X | X | X | X | X | X |
| PAPP-A and HCG |  | X |  |  |  |  |  |  |
| Urine sample | X | X | X | X | X |  |  |  |
| Lung function | X | X | X | X | X | X | X | X |
| Sweat test | X | X | X | X | X |  |  |  |
| Lung CT^1^ | X |  |  |  |  | X | |  |
| Lung MRI^1^ | X |  |  | X |  | X | |  |
| Fetal MRI |  |  |  | X |  |  |  |  |
| EPDS^3^ |  |  |  | X | X |  |  |  |
| Questionnaires^4^ | X | X | X | X | X | X | X | X |
| Semi-structured interview | X |  | X | |  | X | |  |
| Breast milk sample for CFTRm assay^5^ |  |  |  |  | X | X | X |  |
| Key:  X: Planned completion date   1. Lung Imaging – CT will only be performed on non-lactating and non-pregnant participants. Post-partum CT and imaging will be paired, so either a CT and MRI done at the same visit if no longer breastfeeding, or a single MRI if still breastfeeding at 1 year 2. Clinical blood tests – Full blood count, renal profile, liver function, Vitamin A, D, E and K, CRP, OGTT if clinically relevant, HbA1c 3. EPDS – Edinburgh Postnatal Depression Score 4. Questionnaires to include CFQ-R, EQ-5D-5L, PHQ9 and GAD7 5. If breastfeeding whilst taking CFTRm | | | | | | | | |

### Baseline assessments

Screening/baseline assessments are done at the first study visit. There is no separate screening visit.

- Physical examination and history
  - Weight, blood pressure (BP), oxygen saturations, heart rate (HR).
  - Spirometry.
  - Medication list including CFTRm dosages.
  - Review of previous medical history/registry data (if previously consented to having data stored on the CF Trust Registry).
- Clinical tests
  - Sputum microbiology.
  - Sweat chloride.
  - Blood tests – renal function, full blood count, liver function, fat soluble vitamins, sample for CFTRm assay, storage samples of serum and urine (e.g. micro-nutrient analysis, hormonal profile, PAPP-A).
- Questionnaires
  - - CFQ-R
    - EQ-5D-5L
    - PHQ-9 and GAD 7
- Qualitative Experience
  - - Video recorded semi-structured interview.
- Imaging
  - - Paired lung CT/MRI (if enrolled when pregnant – MRI only).

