***Sub-study 1 – ‘Mama’ (pre-conception, pregnancy and parenthood)***

‘Mama’ is a sub-study of pre-conception, pregnancy and parenthood in adult females with CF. This is a prospective, mixed-methods, observational cohort study, collecting data generated in a clinical setting.

Participants will be recruited from the Royal Brompton Hospital (RBH) CF Reproductive and Maternal Health Service, up to 12 months prior to their having confirmed a planned date for actively trying to conceive, with follow-up until two years post-partum.

There will be up to a maximum of eight in-person study visits. These will occur:

- once up to 12 months pre-conception,
- once per trimester of pregnancy (X3), and
- at defined intervals post-partum.

All in-person visits will involve blood tests, lower respiratory tract samples, urine samples, lung function, health and quality of life questionnaires, in addition to taking biological samples for CFTRm assay (blood and breastmilk) and sweat chloride measurements.

The pre-conception, third trimester and 12-month post-partum in-person study visits will include radiological imaging which involves a paired synchronous lung CT and MRI when not pregnant or breastfeeding (or only MRI if visit occurs during pregnancy/lactation). In the third trimester this will also encompass a fetal MRI.

Standardised oral glucose tolerance tests will occur in the second and third trimester visits if clinically indicated (standard of care).

Semi-structured video interviews will be recorded for thematic analysis and will occur:

- once during pre-conception
- once ante-partum, and
- once post-partum.

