# Eligibility criteria

## Inclusion criteria

***Inclusion criteria – ‘Mama’ sub-study:***

- Written informed consent obtained from participant.
- Under the care of Royal Brompton Hospital CF Reproductive and Maternal Health Service
- Age 16 years or above at time of recruitment.
- Confirmed diagnosis of CF.
- Planning a pregnancy or pregnant at time of recruitment.
- Ability to adhere to the required visits and investigations.

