### Oxygen-enhanced Magnetic Resonance Imaging (OE-MRI) of lungs

Up to three oxygen enhanced lung MRIs are proposed:

- 1. prior to conception,
  2. during the third trimester, and
  3. six-months post-partum.

These MRIs will focus on the adult participant’s lungs to assess for any structural or functional changes.

Before the MRI is carried out, the study team will confirm that the participant does not have any contraindications to MRI using the local MRI safety checklist. If the participant is unable to tolerate the MRI for any reason, the procedure will not go ahead. Sedation is not an option for this study.

Headphones will be provided to support increased comfort in the scanning machine. All scans will be performed lying supine, but for the scan in the third trimester this will be a ‘supported supine’ position using pillow/wedges to adjust positioning and improve comfort.

The scan will take 20 – 40 minutes and will involve a short period of breathing 100% oxygen via a facemask. The study team is very experienced in performing oxygen enhanced lung MRI in adults and children and the broader research team has previously performed oxygen enhanced placental imaging via MRI during pregnancy. If any abnormalities are detected on the scan, they will be discussed with the clinical team. Participants will be consented about the risk of false positive or incidental findings. There is no associated radiation risk with MRI, and it can be safely performed in pregnancy.

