### Exploratory endpoints

*‘Mama’ sub-study*

Quantitative endpoints are:

1. Obstetric-specific:
   1. Caesarean section rate
   2. Incidence of medically initiated delivery for pulmonary indication
   3. Incidence of intrahepatic cholestasis
   4. Incidence of pregnancy induced hypertension.
   5. Incidence of pre-eclampsia
   6. Incidence of gestational diabetes
   7. Incidence of large or small for gestational age infants
   8. Incidence of postnatal anxiety/depression (as noted by EPNDS or patient-reported following clinical assessment by other healthcare providers)
   9. Obstetric outcomes according to chronic airways pathogen colonisation history
   10. Obstetric outcomes according to micro-nutritional or early pregnancy hormonal status.
   11. Obstetric outcomes according to diabetes status and therapy (CF diabetes, gestation diabetes, no diabetes)
2. CF-specific:
   1. Incidence of pulmonary exacerbations during pregnancy and within first 24 months requiring oral and/or IV antibiotics.
   2. Variability in lung function during and post-pregnancy as shown by OE-MRI
   3. Sweat chloride levels during pregnancy, and variability per trimester.
   4. Change in weight from pre-conception until pre-delivery.
   5. Change in CFQ-R, EQ-5D-5L, PHQ9 and GAD7 scores.
   6. Bronchial artery size assessment (by MRI) at baseline/pre-conception, antenatal and post-partum (6-12 months).
   7. Change in haemoptysis frequency from baseline, and during pregnancy (as per number episodes per person-years pregnant), and post-partum.
   8. Change in weight according to breast-feeding status in first 24 months post-partum.
   9. Validation of CFTRm assays in serum and breastmilk.

Qualitative endpoints:

1. Thematic analysis of experiences of females with CF throughout:
   1. Family planning,
   2. Pregnancy and childbirth,
   3. Early parenthood.

*Combined ‘Mini’ and ‘Midi’ sub-study*

Exploratory endpoints are:

1. Number of participants with below neonatal birth outcomes:
   1. Prematurity (defined as being born < 37 weeks' gestation)
   2. Low birth weight < 2^nd^ centile
   3. Special care or neonatal intensive care unit admission
2. Frequency of raised blood pressure (>95^th^ centile for age, sex and height on two separate readings)
3. Frequency of faltering growth (definition as per NICE guidelines [NG75])
4. Frequency of delayed development past limit ages in gross motor, vision and fine motor, hearing, speech and language, and social domains. (see appendix 2)

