### Planned recruitment rate

***‘Mama’ sub-study***

The aim of recruitment will be to maximise number of participants in the study. Approximately 15 women complete a pregnancy (give birth to a live infant) a year at the Royal Brompton Hospital CF Maternal Health Service, and patient involvement workshops indicate approximately two-thirds would be inclined to enrol in the trial. Due to the follow up duration we would expect to be able to recruit 20-25 participants.

Participants will be eligible to enrol at any stage in their pregnancy and will be consented for retrospective access to clinical data collected prior to enrolment that is included in the study.

*‘****Mini’ sub-study***

Mirroring the Mama sub-study, with most infants expected to be enrolled via this route, this will provide an overall pool of 15 babies per year. With two-thirds expected to enrol this will lead to around 10 infants per year. Children already born and under the age of 12 months at first visit can also be included which will add an estimated five further infants to the study. Overall, the expected recruitment over 3-year period will be 25 – 35 infants.

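### For women enrolled in the first or second trimester, Section 9.3.2 and the imaging schedule disagree on whether a lung MRI is offered, and Section 15.2.2 lets such a scan count as the pre-conception value for bronchial artery size

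*Protocol*

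**What the plan says.** Four parts of the protocol bear on when a 'Mama' participant has a lung MRI.

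- **Section 9.3.2 (Baseline assessments).** "Screening/baseline assessments are done at the first study visit. There is no separate screening visit". The list of what is done then includes "Paired lung CT/MRI (if enrolled when pregnant – MRI only". No trimester limit is attached.
- **Section 6.1 (Overall design).** "The pre-conception, third trimester and 12-month post-partum in-person study visits will include radiological imaging".
- **Table 1 (Section 9.3.1).** The lung MRI row is marked at pre-conception, third trimester and a merged 6- to 12-month post-partum cell. It is blank for the first and second trimesters.
- **Section 9.3.12 (OE-MRI of lungs).** "Up to three oxygen enhanced lung MRIs are proposed", listed as before conception, third trimester and six months post-partum.

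Who can be at a first visit while pregnant is set by Section 7.1, "Planning a pregnancy or pregnant at time of recruitment", and Section 15.3.2, "Participants will be eligible to enrol at any stage in their pregnancy".

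Two exploratory endpoints in Section 15.2.2 use these scans: "Bronchial artery size assessment (by MRI) at baseline/pre-conception, antenatal and post-partum (6-12 months" and "Variability in lung function during and post-pregnancy as shown by OE-MRI". Section 5.3 states the matching objective for the first as identifying changes in artery size during pregnancy.

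**The concern.** A woman whose first visit is in the first or second trimester is listed for a lung MRI by Section 9.3.2 and for none at that time by Section 6.1, Table 1 and Section 9.3.12. Staff who follow different passages will treat similar women differently. A scan that was not taken cannot be recovered afterwards.

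The second issue is what such a scan is used for. Section 15.2.2 writes baseline and pre-conception as a single time point for bronchial artery size. For a woman enrolled before conception the two are the same. For a woman enrolled in pregnancy they are not: her first scan is taken after pregnancy has begun to act on the measurement. Pooling her value with non-pregnant values blurs the reference against which the objective in Section 5.3 looks for change. If artery size moves steadily in one direction through pregnancy, pooling would make the average change look smaller than it is.

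**Working it through.** No sample size, power or error-rate figure is involved. The check sets the passages side by side and counts lung MRIs by route of entry, assuming that every offered scan is accepted.

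**Step 1. Can a first visit fall in the first or second trimester?** Yes. Section 7.1 admits women already pregnant, Section 15.3.2 sets no limit on stage, and Section 9.3.2 places baseline at the first visit.

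**Step 2. Lung MRIs under each passage.**

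| Enrolled | Section 9.3.2 plus the schedule | Section 6.1, Table 1 and Section 9.3.12 alone |
| --- | --- | --- |
| Pre-conception | 1 + 1 + 1 = 3 (pre-conception, third trimester, post-partum) | 3 |
| First or second trimester | 1 + 1 + 1 = 3 (first visit, third trimester, post-partum) | 1 + 1 = 2 (third trimester, post-partum) |
| Third trimester | 1 + 1 = 2 (first visit is the third-trimester scan, then post-partum) | 2 |

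The columns differ only in the middle row, by 3 - 2 = 1 scan. The ceiling of three in Section 9.3.12 is respected on every route, so the conflict is about timing and not about the number of scans.

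**Step 3. Does any passage settle the conflict?** Section 6.1 adds that imaging is MRI alone when a visit falls in pregnancy or lactation. That sets the modality at the three visits it names; it adds no first- or second-trimester imaging visit. Section 9.3.12 describes positioning for one pregnancy scan only, the third-trimester one.

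**Step 4. What reference does each route give for bronchial artery size?**

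- Enrolled pre-conception: a non-pregnant scan, as the objective needs.
- Enrolled in the first or second trimester: under Section 9.3.2, a scan already in pregnancy; under the other three passages, no scan before the third trimester.
- Enrolled in the third trimester: the first scan and the antenatal scan coincide, so no pre-pregnancy comparison exists.

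Only the first route yields a change from the non-pregnant state. The combined label in Section 15.2.2 does not distinguish the three.

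**Step 5. How many women?** Section 15.3.2 expects 20-25 'Mama' participants. The protocol does not say how many will join before conception or in each trimester, so the number affected cannot be derived: it could be anything from none to most of them.

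**The case against.** The best defence is that the pre-conception column of Table 1 also stands for the first visit. It is the only column that carries consent, eligibility and demographics, and women already pregnant must be consented somewhere. On that reading its MRI mark is the baseline scan, and Section 9.3.2 supplies the rule for women enrolled when pregnant. This is a fair reading of Table 1. It does not rescue Section 9.3.12, which places the first scan before conception, or Section 6.1, which names the pre-conception visit.

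It can also be said that all assessments are optional (Section 6.1). That is true, but optionality lets a woman decline a scan; it does not tell staff whether to offer one.

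A third defence is that assigning a baseline to late enrollees belongs in the statistical analysis plan, which the protocol says will be written before final analysis. In general that is right. Here, however, the protocol's own endpoint wording already merges two different states into one time point, and a plan that follows it would inherit the merger.

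Several stronger readings that a reader might infer are not supported:

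- **That early-pregnancy scans would be unplanned or hazardous.** Section 9.3.2 itself plans them, and Section 9.3.12 states that MRI can be done safely in pregnancy. The point alleges no harm.
- **That a third-trimester enrollee would be given a change of exactly zero.** This would need one scan to be entered as both baseline and antenatal value. The protocol specifies no such analysis.
- **That the OE-MRI variability endpoint is distorted in the same way.** It names no baseline and covers the time during and after pregnancy, so an early-pregnancy scan lies within its stated window.

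**Conclusion.** The point holds, as a minor one. For enrolment in the first or second trimester the protocol gives two incompatible answers on whether a lung MRI is offered at the first visit, a difference of one scan per woman. Separately, the bronchial artery endpoint allows a first scan taken in pregnancy to be pooled with non-pregnant scans, although its objective is change during pregnancy. For third-trimester enrolment there is no pre-pregnancy value to compare with.

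The reach is limited. The endpoint is exploratory and will be summarised descriptively, no sample-size claim rests on it, and no primary endpoint uses these scans. The count of women affected, out of the 20-25 expected, is unknown. The conclusion rests on reading the pre-conception wording of Sections 6.1 and 9.3.12 as written. The direction of any dilution further assumes that artery size changes steadily through pregnancy, which the documents do not establish.

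**What to change.** 1. Reconcile Section 9.3.2 with Section 6.1, Table 1 and Section 9.3.12, so that all four give the same answer for women enrolled in pregnancy. The choice of imaging schedule is for the study team. Check that the participant information sheet agrees with the result.
2. In Section 15.2.2, separate baseline from pre-conception in the bronchial artery endpoint. Use pre-conception scans as the reference for change in artery size, and report scans first taken in pregnancy separately, by trimester at the time of the scan.
3. Record the stage of pregnancy at enrolment and at each scan, and show in the report how many women contribute to each summary.

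The cost is a wording amendment. Women without a pre-conception scan leave the change summary of one exploratory endpoint. In a small cohort that is a real loss, of a size the documents do not allow one to state, but their scans are still reported. The amendment is best made before scans accrue.

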### Medical History

For adult participants who are patients under the Royal Brompton CF service, permission to access past medical details from medical records (including from the UK CF Registry if participant has previously consented to this) will be requested to be used in analysis of the study results.

